#### Nurse Outcomes

Change in nurses risk factor management confidence, attitudes and practice scores between early and late intervention services (comparison) will be assessed for clustering and, if this is not significant, comparison will be made between the change in early and late intervention providers using unilevel multivariate methods.

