## Methods/Design

### Study Design and Setting

This quasi-experimental study is being conducted in GCN services in the state of NSW, Australia. Within Australia, GCNs can be either registered or enrolled nurses who perform a diversity of roles depending on the service in which they work. The role has traditionally focused on providing a range of nursing care in people's homes such as assisting with activities of daily living, wound management, chronic disease care, continence management, palliative care, medication management, disability and dementia care. Coordination of care with other service providers and health promotion has also traditionally been a major part of their role.

A quasi-experimental design was chosen because it was not feasible to randomise the intervention according to individual patient or practitioners within the services. GCN services have been randomly allocated to an 'early intervention' group or 'late intervention' (comparison) group. 'Early intervention' services are provided with training and support for nurses in identifying and offering brief SNAP intervention for clients during routine consultations (see service-level intervention). Data is being collected from clients in both groups at baseline, three months and six months to examine short and medium term change in SNAP risk factors. This will enable a comparison of client outcomes between early and late intervention groups. After the six month data collection point the 'late intervention' group will be offered the same training and support as the early intervention group.

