### Power and Sample Size Calculation

The sample size calculation is based on the primary outcomes of change in continuous self reported measures of lifestyle risk factors rather than differences in proportion of individuals in each risk category (secondary outcomes). There is evidence that risk associated with diet, physical activity and weight is continuous [20-22]. Achieving a shift in risk categories is more difficult to demonstrate in the context of a brief intervention and would require a very large sample size which is beyond the scope and resources of this trial. Hence the focus is on change in continuous measures of lifestyle risk factors as the primary outcomes.

A sample size of 360 clients in each group (total n = 720) is required to have 80% of power to detect the following difference between intervention and comparison groups:

▪ Mean difference of 1 serve of fruit and vegetables consumed (equivalent to 22% increase in the 'early intervention' group);

▪ Mean difference of 1.2 for physical activity scores as measured by a validated brief physical activity assessment tool [23] (equivalent to a 29% increase in mean scores in the 'early intervention' group);

▪ Mean difference of 0.6 for alcohol risk scores as measured by the AUDIT-C tool [24] (equivalent to a 10% reduction in mean scores in the 'early intervention' group);

▪ Mean difference of 4.1 kg in self reported weight (equivalent to a 4.4% weight reduction in the 'early intervention' group).

This is based on 5% significance level and 80% power (β = 0.8 and α = 0.05) allowing 20% lost to follow-up and a design effect of 1.8 due to clustering. The expected differences between intervention and comparison groups has been estimated based on previous research [25]. These differences are also considered meaningful from a population health perspective. Baseline prevalence of risk factors is based on NSW Health Survey 2006 for individuals aged 45-74 years [26].

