### Recruitment

#### Generalist Community Nursing Services

Four GCN services were recruited to participate in the trial. An expression of interest to participate in the trial was sent out to all seven Area Health Services(AHS) in NSW. In NSW, AHS are responsible for providing all hospital-and community-based health care apart from general practice and PHC services for specific population groups such as Aboriginal and Torres Strait Islanders. AHS were asked to nominate suitable GCN services which were ranked and selected according to the selection criteria provided in Table 1.

**Table 1 T1:** Selection criteria for recruiting generalist community nursing services to participate in the trial

Types	Selection Criteria
**Inclusion Criteria**	The team deliver GCN services to clients between 30 and 80 years of age The team is able to recruit sufficient numbers of eligible clients into the study in a given recruitment period (based on trial sample size calculation). The individual clinicians are interested in participating and commit to undertaking training and intervention Willingness of the service to accommodate a recruitment officer to work on site to identify and contact potentially eligible clients from client referrals. Willingness of the service to review and modify service assessment protocols to include standard tools for identification SNAP risk factors (if not already included). The team/services has the capacity to participate in SNAP training The team/service has the capacity to deliver SNAP intervention to a given number of clients in a given intervention period. The team/service is broadly representative of community nursing services statewide (choosing 'typical service(s)'). Willingness of the service to participate in project management meetings with study management team body to support the trial implementation (eg service manager and AHS project/recruitment officer).

**Exclusion Criteria:**	Teams/services undergoing concurrent changes in management, structure or service deliver that would impact on capacity to be involved in the trial. Involvement in other service development activities that may contaminant trial activities (eg concurrently delivering self management program for clients).

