#### Service-Level Intervention

At the service-level, the intervention aims to increase the capacity of the GCN to undertake a brief SNAP intervention with clients. The design of the intervention has been informed by our previous research reporting on a theoretical model of the factors shaping the lifestyle risk factor management practices of non GP PHC providers [27]. The model suggests lifestyle risk factor management practices are shaped by: 1) clinician commitment, in particular beliefs about role congruence, client receptiveness and outcome expectations; and 2) clinician capacity, including self-efficacy, role support (provision of training, decision support tools, client education materials and linkages to referral services) and the extent to which lifestyle risk factor management activities fit with clinicians' way of working.

Specifically, the service-level intervention comprises of the following components:

▪ A one day training program for participating nurses delivered by the research team in conjunction with local providers. The training specifically focus on building clinician knowledge, skills and positive attitudes relevant to the model constructs, with a particular focus on developing behaviour change skills such as motivational interviewing and goal setting (learning objectives detailed in Table 3). An emphasis is placed on experiential learning including the use of role-plays with simulated clients (actors), group discussions and activities, which have been shown to be effective in improving knowledge, skills and confidence related to lifestyle risk factor management [28-31].

▪ The integration of standard screening tools and prompts for SNAP risk factors (see additional file 1) into the service specific assessment process used by the nurses (see additional file 1).

▪ The development and dissemination of a local service referral directory to each GCN team to promote referral of clients for ongoing specialist management or more/ongoing intensive lifestyle intervention (such as the proactive telephone Quitline).

▪ The provision of resources to support the implementation of the intervention including a written guide for nurses, written action plans for use with clients on each SNAP risk factor, tape measures for measuring waist circumference, and pedometers to loan out to clients to encourage self monitoring of incidental physical activity

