### Late Intervention (comparison) group

Two of the four GCN services have been randomly allocated to the 'late intervention' condition. These services will not receive the study intervention till after the six month data collection point and continue to deliver 'usual care'. This will enable the effectiveness of the service and client level intervention to be assessed in comparison to usual practice.

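### Nurse outcomes: a non-significant clustering test is allowed to remove service from the analysis, although services were allocated two per arm, so the fallback p-values can be too small

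*Protocol article*

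**What the plan says.** The Nurse Outcomes part of the Statistical Analysis section states that change in nurses' scores "will be assessed for clustering and, if this is not significant, comparison will be made between the change in early and late intervention providers". The tool named for that fallback is a single-level one: the sentence closes with "using unilevel multivariate methods". The article thus fixes a rule: no significant clustering, then nurses are compared as independent observations.

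The design sections set the context. "Four GCN services were recruited to participate in the trial", and "Two of the four GCN services have been randomly allocated to the 'late intervention' condition", which leaves two services in each arm. Study Design and Setting explains that "it was not feasible to randomise the intervention according to individual patient or practitioners within the services". Parts of the intervention reach nurses as a team, for example "The development and dissemination of a local service referral directory to each GCN team". For clients, the sample size section takes clustering as given, "allowing 20% lost to follow-up and a design effect of 1.8 due to clustering".

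Table 4 lists nurse assessment and management scores as a secondary outcome, and nurse confidence and attitudes as mediators.

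**The concern.** Failing to reject the absence of clustering is not evidence that it is absent. When whole services are allocated, the arm difference carries any difference between services, whether or not a test detects it. With two services per arm, only 2 df inform the spread between services within arm, so the test is weak where it is needed. If it misses real clustering, the plan moves to an analysis whose standard error leaves out the service component.

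At stake are the claims about nurse practice, confidence and attitudes. The Discussion expects clinician-level findings to inform nursing roles, training and investment.

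**Working it through.** The article states no sample size, power or error rate for nurse outcomes, so there is no figure of its own to reproduce.

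**Inputs from the article.** Four services, two per arm; allocation by service; a significance test for clustering; single-level analysis if it is not significant. "This is based on 5% significance level and 80% power" is stated for the client sample size.

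**Assumptions.** 10, 15 or 30 nurses per service (m); ICC of the change score from 0 to 0.10; clustering test at 5%; service-level t-test on 2 df when clustering is significant; two-sided 5% group comparison; equal service sizes; normal scores.

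**Step 1: power of the within-arm clustering test.** For the one-way random-effects F test of services within arm,

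power = P[ F(2, 4(m−1)) > Fcrit × (1−ICC) / (1+(m−1)ICC) ].

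For m = 15 and ICC 0.05: Fcrit(2, 56) = 3.162; (1−0.05)/(1+14×0.05) = 0.95/1.70 = 0.559; 3.162 × 0.559 = 1.767; P[F(2, 56) > 1.767] = 0.180. The test misses this clustering in 82% of trials.

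**Step 2: false-positive rates with no true effect.** Simulation, 200,000 runs per setting. Entries are percentages for 10 / 15 / 30 nurses per service.

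| ICC | Clustering detected (2 df) | Single-level test, given a non-significant 2-df test | Whole procedure, 2-df test | Whole procedure, 3-df test across all four services |
|---|---|---|---|---|
| 0 | 5.0 / 5.0 / 5.0 | 5.1 / 5.0 / 5.1 | 4.8 / 4.7 / 4.8 | 3.5 / 3.5 / 3.4 |
| 0.005 | 5.7 / 6.1 / 7.3 | 5.5 / 5.8 / 6.7 | 5.2 / 5.5 / 6.2 | 3.8 / 3.8 / 4.2 |
| 0.01 | 6.5 / 7.3 / 9.9 | 6.0 / 6.5 / 8.4 | 5.7 / 6.1 / 7.6 | 4.0 / 4.2 / 4.8 |
| 0.05 | 13.3 / 18.0 / 30.7 | 10.6 / 13.7 / 21.5 | 9.2 / 11.2 / 14.9 | 5.7 / 6.3 / 6.9 |
| 0.10 | 22.7 / 31.3 / 49.4 | 16.4 / 21.9 / 33.9 | 12.6 / 15.1 / 17.1 | 6.8 / 7.0 / 6.9 |

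A service-level t-test used throughout (critical t = 4.30 on 2 df) stays at 4.9-5.1% in every setting.

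**Step 3: does passing the 2-df test protect?** At ICC 0.05 and 15 nurses per service, the single-level test is falsely positive in 13.7% of trials that pass, against 13.6% with no pre-test. In this model the spread between services within arm is independent of the arm difference, so passing says nothing about whether service effects created that difference. The 3-df test includes the arm difference, which is why it inflates less; for the same reason it counts a real intervention effect as clustering.

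**Step 4: power if service is always kept.** For 15 nurses per service in SD units, the standard error of the arm difference is √(ICC + (1−ICC)/15). At ICC 0 this is √(1/15) = 0.258; at ICC 0.05 it is √(0.05 + 0.95/15) = 0.337. For a 0.5 SD effect the noncentrality is 0.5/0.258 = 1.94 or 0.5/0.337 = 1.49, giving power of 21% or 15% on 2 df. For 0.8 SD it is 3.10 or 2.38, giving 40.5% or 28%.

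**The case against.** The strongest reply is about size. The article names neither the form nor the level of the clustering test, and its wording also fits a test across all four services. On that reading the overall error is about 6-7% at ICC 0.05-0.10 and below 5% at ICC 0.01 or less. A 2-df test at a lenient 20% level gives 8.3% (ICC 0.05) and about 10% (ICC 0.10) with 15 nurses per service. The service-level t-test in the significant case is also assumed.

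The only clustering figure in the article, the client design effect of 1.8, implies a small ICC: (1.8−1)/(180−1) = 0.0045 at 180 clients per service, or 0.8/(144−1) = 0.0056 after 20% loss. At such values the inflation is slight. Change scores may also have a low ICC, because stable service differences partly cancel. All this stands as a limit on magnitude. The client figure need not apply to nurses, who share training and management within a service, so it settles the nurse ICC in neither direction.

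A reader might infer that the test almost never finds clustering, or that the nurse p-values are bound to be too small. The article supports neither: detection reaches 49% at ICC 0.10 with 30 nurses per service, and with little clustering or a 3-df test the error can be at or below 5%. Nor does the rule touch the main result: the primary outcomes all come from the client survey and have their own analysis.

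What survives is the rule itself. It is a stated method, not a detail left to an analysis plan, and non-significance on so few df cannot justify treating nurses as independent.

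**Conclusion.** The point holds, with its size left conditional. The rule lets a weak test decide whether the unit of allocation stays in the analysis. With a within-arm 5% test, 10-30 nurses per service and a service-level t-test as the alternative, the nominal 5% becomes 9-15% at ICC 0.05 and 13-17% at ICC 0.10, but only about 5-8% at ICC 0.005-0.01. With a test across all four services it is about 6-7% at ICC 0.05-0.10, with no inflation at ICC 0.01 or below. That the rule is unsound does not depend on these choices; how much it inflates error does. The consequence is confined to the nurse secondary and mediator outcomes, so this should be corrected but does not threaten the primary comparison.

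**What to change.** Remove the clustering test as a decision rule. State that nurse change scores will always be analysed with service retained: either service means compared on 2 df, or a mixed model with a service random effect and small-sample degrees of freedom. Report the ICC with its interval as a description only.

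The edit is one sentence, but the cost in power is real. With 15 nurses per service, as ICC goes from 0.05 to 0, power is about 15-21% for a 0.5 SD effect and 28-41% for 0.8 SD. That follows from having four services. If the sponsor finds it too low to be useful, present the nurse comparison as descriptive, with estimates and no confirmatory p-value.

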### Qualitative Evaluation

As this is a complex intervention delivered within the context of normal practice, a qualitative evaluation of the implementation process is important in interpreting the study findings [44]. A qualitative evaluation will specifically explore the acceptability, usefulness and sustainability of the study intervention for both GCNs and participating clients.

It is proposed that nurse focus groups be conducted in each early intervention service along with individual interviews with team managers and project officers (n = 8) to explore the:

▪ experience of implementing SNAP risk factor management in routine practice (appropriateness, feasibility, client receptiveness, factors affecting implementation);

▪ usefulness of components of the intervention and additional supports required for sustained uptake;

▪ sustainability of the intervention and issues to consider in transferring to other GCN teams

Semi-structured telephone interviews will also be conducted with a sample of clients (n = 20-25) from early intervention sites who recall receiving lifestyle intervention from a GCN. Clients will be purposefully sampled according to age, gender, health and socio-economic status of clients. The interviews will aim to explore:

▪ acceptability of SNAP screening;

▪ acceptability and usefulness of the brief lifestyle intervention provided by the community nurse;

▪ acceptability and usefulness of referral to support services.

All interview and focus group data would be transcribed verbatim and subject to thematic analysis using Nvivo 8 [45] to identify convergence and divergence of themes.

### Ethics

The project was approved by the UNSW Human Research Ethics Committee (HREC) and the HREC in each AHS. All participants are requested to provide their informed consent.

## Discussion

Lifestyle risk factors need to be tackled at multiple levels including individual intervention provided by health professionals as well as through population health approaches. Much of the focus in health professional interventions to date has been on general practitioners, with relatively little attention paid to nurses outside of general practice. Community health nurses are well placed to deliver lifestyle interventions to clients and their involvement should make these types of intervention more accessible to the population, but little is known about the effectiveness of such interventions delivered in routine practice.

This study is a complex intervention trial examining the effectiveness lifestyle risk factor management delivered by GCNs. The trial is unique in that it is being delivered as part of routine practice (without additional nurse resources) and aims to examine the impact of brief intervention on multiple lifestyle risk factors. The collection of quantitative outcome data will provide new information about the efficacy of such an approach at both the clinician and client level. This will be supplemented by the qualitative evaluation which will provide important contextual information about the feasibility, acceptability and sustainability of this approach for both nurses and clients. Together this information will help inform future community nursing practice and PHC policy including:

• defining the roles of GCNs in assessing and intervening with clients to modify lifestyle risk factors

• identifying competencies for vocational training and continuing education of GCNs

• organisation of care and the place of health promotion interventions in the care pathway for GCN clients

• investment in health promotion programs involving GCNs

• the role of referral pathways linking PHC with support services for lifestyle risk factor management including both public and private providers

The findings and intervention materials of the study will be disseminated using a knowledge transfer exchange strategy. This will include dissemination of key findings using peer reviewed journals, conference presentations, the formulation of simple research summaries tailored for practitioner, service managers and policy makers.
